### Masking

As to the characteristics of the interventions under evaluation, those who measure the results and who will analyze the data will be blind. To ensure that the blind participant who measures the results will be someone other than the health professional applying SSC, that person will not be in the delivery room and will apply the study measurements to all newborns treated at the clinic without knowledge of whether or not they are study participants.

The person conducting the analysis will be given the database in which the variable that identifies whether the research subject belongs to the control group or the intervention group is found; this will then be coded and the code that identifies them will not be available to the analyst.

### Statistical methods

Descriptive analyses were performed using measures of central tendency (median, average), location (percentiles) and dispersion (standard deviation and ranges) for continuous variables and absolute frequencies and relative for the categories. Bivariate analysis will be performed to determine which variables (evaluation interventions and others) are associated with exclusive lactancy at 6 months. In the continuous variables, the Student’s *t* test will be used for independent samples or the Wilcoxon rank sum test when the assumptions of normality for the *t* test are not fulfilled. The assumption of normality will be evaluated with the Shapiro-Wilk and Kolmogorov-Smirnov tests. Contingency tables will be constructed in the categorical variables, assessing the independence between variables with the chi-square test, or Fisher’s exact test when the assumption of number of cases per cell in the contingency tables, multiplied by two, is not fulfilled. The relative risk (RR) will be calculated as an effects measurement with confidence intervals, adjusted measurements will be calculated using a multivariate Poisson regression model, for adjustment variables with significant results those with biological plausibility will be used in the bivariate analysis. An analysis will be carried out for a two-tailed type I error level of 5 %. The Stata 11 program will be used for the data analysis. An interim analysis will be performed upon submission of half of the expected events (106), setting the limits for early termination of the trial according to the methods proposed by Pampallona and Tsiatis 1994 [21].

The protocol study information will be revised by the Data Monitoring Committee used by the clinic and recruited for the study. This committee will assess the study’s progress, safety data, and critical efficacy endpoints. The DMC reviews unblinded information during the conduct of the study. The information will be periodically revised every 2 weeks.

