**Methods/design:**

A randomized, blind clinical trial will be performed with full-term healthy newborns born at the Universidad de La Sabana Clinic. The blind trial participants will be those persons measuring the results and analyzing the data. The sample size will be calculated for a type I error of 5 %, a two-tailed type II error of 20 %, and an estimated percentage loss of 30 %; 150 infants will be included in each group. Randomization will be performed using permuted, size-6 blocks. Descriptive analysis will be conducted using central tendency and dispersion measurements. A bivariate analysis will be performed to determine which variables are associated with exclusive lactancy at 6 months. For continuous variables, Student’s *t* test will be used for independent samples, and the Wilcoxon rank sum test will be used if the assumptions of normality for the *t* tests are not fulfilled. The assumption of normality will be evaluated using the Shapiro-Wilk and Kolmogorov-Smirnov tests. Categorical variables in contingency tables will be constructed to assess the independence between variables using the chi-square test, or Fisher’s exact test when the assumption of the number of cases is not met by the values in the contingency tables multiplied by two. This will be calculated as a measurement of the effect of relative risk (RR) with confidence intervals; the adjusted measurements will be calculated using a multivariate regression Poisson model. Variables with significant results will be used in the bivariate analysis, and those with biological plausibility will be used for the adjustment. The analysis will be carried out for a two-tailed type I error level of 5 %. The Stata 11 program will be used for data analysis. An interim analysis will be performed upon the submission of half the expected events (106), setting limits for the early termination of the trial according to the method proposed by Pampallona and Tsiatis (1994). Intervention: There will be two SSC randomization groups: early versus immediate. After completing the neonatal adaptation process and based on the group assignment, the mother will be left with her newborn child in hospital accommodation. Prior to discharge, the Infant Breast-Feeding Assessment Tool (IBFAT) will be applied. Monitoring will initially be performed with a face-to-face assessment between 3 and 10 days of life, followed by monthly telephone calls for 6 months to verify lactation status.

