### Objectives

To determine the effect of immediate versus early SSC birth on the duration of exclusive human lactancy in healthy, full-term newborns in the Universidad de La Sabana Clinic.

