### Hypothesis

○ Null hypothesis: there is no difference in the percentage of healthy, full-term newborns receiving exclusive human breastfeeding for three or more months between the immediate versus early birth SCC groups: relative risk (*RR*) = 1○ Alternative hypothesis: there is a difference in the percentage of healthy, full-term newborns receiving exclusive human breastfeeding for three or more months between the immediate versus early birth SCC groups: *RR* ≠ 1

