#### Outcomes

##### Primary outcome

Exclusive human lactancy for three or more months: exclusive human lactancy is defined as the time in months with human lactation as the only food source and without having received other liquids or solid foods (except drugs and/or vitamins).

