### Sample size

24 % babies in Colombia, received exclusive breastfeeding up to 5 months old (9). This was the baseline risk assumed for the sample size calculation [9]. No studies were found that comparing different strategies from SSC; so that estimate the sample size, information 2014 Cochrane meta-analysis was used [3], which compares SCC (regardless of the starting time) with nonintervention. In this meta-analysis, SSC increases exclusive human lactancy in babies of 3 − 6 months of age (RR 1.97, 95 % CI 1.37 to 2.83). With the information of exclusive breastfeeding for Colombia and the effect of SCC﻿, report in the meta-analysis, was estimated ﻿a sample size of 300 newborns. This sample was calculated, two tailed, for a type I error of 5 %, a type II error of 20 %, and an estimated loss rate of 30 %. Will be included 150 newborns per study group.

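### The hypothesis and primary outcome are set at three or more months of exclusive lactation, but the only time point the analysis text names is 6 months

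*Protocol article*

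**What the plan says.** All references are to the protocol article.

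- **Objectives:** "To determine the effect of immediate versus early SSC birth on the duration of exclusive human lactancy". No cut-off is given.
- **Hypothesis:** null and alternative concern the percentage of newborns "receiving exclusive human breastfeeding for three or more months between the immediate versus early birth SCC groups", as RR = 1 against RR ≠ 1.
- **Primary outcome:** "Exclusive human lactancy for three or more months", with exclusive lactancy then defined as a time in months.
- **Secondary outcomes:** IBFAT feeding capacity, maternal satisfaction, weight in the first week, and hospitalisation in the first week. Six-month exclusivity is not listed.
- **Sample size:** 24 % of "babies in Colombia, received exclusive breastfeeding up to 5 months old" is the baseline. The effect is a relative risk of 1.97 from a meta-analysis in which "SSC increases exclusive human lactancy in babies of 3 − 6 months of age".
- **Statistical methods:** "Bivariate analysis will be performed to determine which variables (evaluation interventions and others) are associated with exclusive lactancy at 6 months". The relative risk with confidence intervals, the adjusted Poisson model, the two-tailed 5 % level and the interim analysis at 106 events follow in the same paragraph, none with its own time point.
- **Abstract, Methods/design:** "A bivariate analysis will be performed to determine which variables are associated with exclusive lactancy at 6 months".
- **Instruments and times; Follow-up:** monthly telephone calls for 6 months.

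**The concern.** The outcome that the analysis text names is not the outcome that the hypothesis and the primary-outcome section declare. The 6-month wording appears in both the abstract and the methods, and in the methods the randomised interventions are among the variables to be related to 6-month status. An analyst who follows that sentence literally would analyse a different endpoint from the declared one.

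The two endpoints are not interchangeable. Infants still exclusively breastfed at 6 months are a subset of those who reached three months, so the event rate is lower at 6 months, and the relative risk and the power can differ. The interim analysis counts events without saying which status, at which age, is an event, so it inherits the ambiguity.

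**Working it through.** **1. Time points side by side**

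| Section | Time point |
|---|---|
| Objectives | duration, no cut-off |
| Hypothesis | three or more months |
| Primary outcome | three or more months |
| Secondary outcomes | no exclusivity endpoint |
| Sample size, baseline 24 % | up to 5 months |
| Sample size, RR 1.97 | ages 3 to 6 months |
| Statistical methods, bivariate analysis | 6 months |
| Abstract, bivariate analysis | 6 months |
| Statistical methods, RR and Poisson model | none given |
| Statistical methods, interim events | none given |

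The declared endpoint appears in two sections and in no analysis sentence. The analysed endpoint appears in two analysis sentences and in no outcome list.

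**2. Does the sample size identify the intended time point?** Inputs from Sample size: control 0.24; intervention 0.24 × 1.97 = 0.4728; two-sided 5 %; 80 % power; 30 % loss. The pooled-variance formula is

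n = [1.960 × √(2·p̄(1−p̄)) + 0.842 × √(p₁(1−p₁) + p₂(1−p₂))]² / (p₂−p₁)², with p̄ = 0.3564.

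This gives 66 per arm, and 66/0.70 = 95 after loss. With continuity correction it is 74, and 74/0.70 = 106. Neither is the stated 150 per arm. At 24 % against 47.28 %, power is 95 % with 105 evaluable per arm (150 × 0.70) and 99 % with 150. So the stated 300 is not reproduced, though it exceeds what these inputs require. That is a separate matter. For this point, the calculation does not reveal a 3-month or a 6-month design.

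**3. Does the interim figure of 106 identify it?** Using the same rates, total expected events are 150 × (0.24 + 0.4728) = 106.9 with no loss, or 105 × 0.7128 = 74.8 after loss. The figure is also half of 212, the continuity-corrected total after loss (148/0.70, rounded up). It can be reached in more than one way and does not fix the time point.

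**4. Can a power difference be stated?** Not from the article, which gives no 3-month or 6-month rate. As a sensitivity only, with RR 1.97, 105 evaluable per arm and *assumed* control rates:

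| Assumed control rate | Power |
|---|---|
| 10 % | 51 % |
| 15 % | 72 % |
| 20 % | 87 % |
| 24 % (stated, 5 months) | 95 % |
| 30 % | 99 % |

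Power depends on the rate at the chosen age, but the article does not say where on this scale either endpoint lies.

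**5. What if both time points were tested and the better one reported?** For nested yes/no endpoints with rates p₃ and p₆, the correlation is ρ = √[p₆(1−p₃) / (p₃(1−p₆))]. The chance that at least one |z| exceeds 1.96 under the null comes from the bivariate normal distribution with that ρ. Over *assumed* ranges of 35–50 % at 3 months and 15–20 % at 6 months:

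- 35 % and 20 %: ρ = √(0.20 × 0.65 / (0.35 × 0.80)) = 0.68; type I error 8.4 %.
- 50 % and 15 %: ρ = √(0.15 × 0.50 / (0.50 × 0.85)) = 0.42; type I error 9.3 %.

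**The case against.** The strongest defence is that only one primary outcome is declared and that the hypothesis, stated as a relative risk, matches it. The relative-risk sentence in Statistical methods has no time point, so it can be read as the test of that hypothesis. Participants are to be analysed by randomised group at a two-tailed 5 % level. On this view the 6-month phrase is a slip in one descriptive sentence, repeated in the abstract.

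Most of this stands, and it limits the point. Three stronger readings are not supported:

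- **That the hypothesis is never tested, or that a 6-month headline could be substituted freely.** The relative-risk sentence may be its test, and a 6-month headline would visibly depart from the declared primary outcome. The article does not plan to test both and choose.
- **That 5 months is a third endpoint.** Only the 24 % baseline is at that age. The relative risk covers 3 to 6 months, which includes the three-month endpoint. A rate at a nearby age is an approximate planning input.
- **That the 6-month analysis is shown to be underpowered.** This needs rates or effects that the article does not give. A constant cessation hazard through 24 % at 5 months implies 0.24^(6/5) = 18 % at 6 months. At the planned RR of 1.97 with 105 per arm, power is then 82 %, which meets the planned 80 %. That curve also fits poorly with the 1.8-month national average quoted in the Background: it implies a mean of 5/ln(1/0.24) = 3.5 months.

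The defence does not remove the contradiction. The relative-risk sentence follows the 6-month sentence in the same paragraph, and its adjustment variables are tied to that bivariate analysis, so 6 months is at least as natural a reading. Nor can 6 months be treated as a planned secondary analysis, since it is not on the secondary list. A separate analysis plan could add detail, but the published text would still disagree with itself.

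**Conclusion.** The point holds as an internal contradiction. The declared hypothesis and primary outcome are at three or more months. The only time point in the analysis text, in both methods and abstract, is 6 months, which is not a listed outcome. The relative-risk sentence and the interim event count leave the time point open, and the sample-size baseline is not at 3 months either. This conclusion rests on the wording alone and on no calculation.

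No loss of power can be attached to it, because the needed rates are not given. The type I error of about 8.4 to 9.3 % describes only the case in which both time points are tested and the better one reported, and it depends on the assumed rates. It shows why one time point should be fixed in advance and does not describe what the article proposes. Because the primary analysis determines what the trial can conclude, the text should be aligned before recruitment opens.

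**What to change.** 1. In Statistical methods and in the abstract's Methods/design text, name one primary analysis: immediate versus early SSC, proportion exclusively breastfed for three or more months, relative risk with 95 % confidence interval, two-sided 5 % level.
2. Label exclusivity at 6 months as secondary and add it to the Secondary outcomes list.
3. Define the interim event at the three-month endpoint and restate the event count on that basis.
4. In Sample size, either use a 3-month baseline rate or state that the 5-month rate serves as a proxy.

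The cost is a wording change in a few paragraphs, plus a recalculation if a 3-month baseline is adopted. The Trials status section says recruitment has not opened, and the monthly calls already capture status at both 3 and 6 months, so no new data or visits are needed.

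### The adjusted RR rests on an unclear, partly significance-driven covariate rule screened at 6 months rather than 3, and the Poisson variance for a yes/no outcome is left open

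*Protocol article*

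**What the plan says.** The Statistical methods section plans a crude effect first: "The relative risk (RR) will be calculated as an effects measurement with confidence intervals", with chi-square or Fisher tests. It then adds that "adjusted measurements will be calculated using a multivariate Poisson regression model", in Stata 11. The abstract (Methods/design) says the same: "the adjusted measurements will be calculated using a multivariate regression Poisson model". Neither place names a variance estimator.

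The covariate rule appears twice, in different words:

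- Abstract: "Variables with significant results will be used in the bivariate analysis, and those with biological plausibility will be used for the adjustment".
- Statistical methods: "for adjustment variables with significant results those with biological plausibility will be used in the bivariate analysis".

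The bivariate analysis that supplies these variables is meant to find which of them "are associated with exclusive lactancy at 6 months". The primary outcome, however, is "Exclusive human lactancy for three or more months", and the Hypothesis section uses the same three-month cut. In Statistical methods the only breastfeeding outcome named is the 6-month one.

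**The concern.** There are three weaknesses, all in the same short paragraph.

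**Data-driven adjustment.** If significance in the trial's own outcome data decides what enters the model, the adjusted RR depends on choices made after the data are seen. The candidates are not restricted to baseline. The trial records IBFAT, maternal satisfaction, first-week weight change and neonatal unit admission, all after the intervention has begun. Each could predict exclusive breastfeeding and also pass as biologically plausible. If early skin-to-skin contact works partly through better early feeding, adjusting for IBFAT would remove part of the effect under study.

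**Wrong time point.** Covariates screened against the 6-month outcome need not be the ones that matter at three months. As the section reads, it is also unclear which outcome the adjusted model is for.

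**Variance.** A Poisson model with a log link estimates the RR for a yes/no outcome properly. Its model-based variance, however, is p where the binomial variance is p(1 − p). With a common outcome the difference is material: intervals come out too wide and the adjusted test loses power. The adjusted result could then miss significance where the crude test finds it, for a purely technical reason.

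**Working it through.** **1. The covariate rule, read side by side.** Three readings are possible:

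- Significant or plausible variables are adjusted for. Significance alone is then enough.
- Significant variables are adjusted for only if also plausible. Significance is then necessary.
- Taken literally, the abstract sends significant variables to the bivariate analysis and plausible ones to the adjustment. But significance is known only after the bivariate analysis has been run, so this reading is circular.

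The Statistical methods sentence links adjustment, significance and plausibility in yet another order. No reading yields a fixed list, and none excludes post-birth variables.

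**2. The variance.** The plan states no standard error or interval width, so there is no figure of its own to reproduce.

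Inputs from Sample size:

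- Control rate p0 = 0.24. The source figure is for babies who "received exclusive breastfeeding up to 5 months old", so using it at three months is an assumption.
- RR 1.97, so p1 = 0.24 × 1.97 = 0.4728.
- 150 per arm with 30% loss, so n = 150 × 0.70 = 105.

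Formulas for the standard error (SE) of log RR:

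- Model-based Poisson: √[1/(n p0) + 1/(n p1)]
- Binomial, which the robust estimator targets: √[(1 − p0)/(n p0) + (1 − p1)/(n p1)]

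Design rates, n = 105 (n p0 = 25.2, n p1 = 49.644):

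- Model-based: √(0.03968 + 0.02014) = 0.2446. The 95% CI around 1.97 is 1.22 to 3.18.
- Binomial: √(0.03016 + 0.01062) = 0.2019. The 95% CI is 1.33 to 2.93.
- Ratio of log-scale widths: 0.2446/0.2019 = 1.21.

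With all 150 per arm followed up, the intervals are 1.32 to 2.94 and 1.41 to 2.74. The ratio is again 1.21, because n cancels.

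Equal rates p in both arms: the ratio reduces to 1/√(1 − p). At p = 0.24 it is 1/√0.76 = 1.147. The nominal critical value 1.96 then acts as 1.96 × 1.147 = 2.248, and the two-sided type I error is about 2.5%.

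Range over other common rates (assumptions, except 24%):

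| Rate in both arms | Excess log-scale width | Type I error |
|---|---|---|
| 15% | 8.5% | 3.4% |
| 24% | 15% | 2.5% |
| 30% | 20% | 1.9% |
| 40% | 29% | 1.1% |
| 47.3% | 38% | 0.7% |

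**3. Does it persist with a covariate in the model?** Poisson models were fitted to 1,500 simulated trials per scenario with one assumed covariate, comparing model-based with robust variance at 105 per arm:

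- 24% in both arms: intervals about 15% too wide; type I error 2.4% vs 5.1%.
- 24% vs 47.3%: about 22% too wide; power 88% vs 95%.
- 24% vs 36% (assumed smaller effect): about 20% too wide; power 32% vs 47%.

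At 150 per arm with 24% in both arms, the type I error was 2.8% vs 5.1%.

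**The case against.** A reader might infer that the plan uses ordinary Poisson standard errors and that its intervals are therefore too wide. The documents do not support this. They name the model and are silent on the variance. A software option of that kind may well sit in the full protocol or analysis plan, and with robust variance the excess disappears. The variance point is therefore conditional. A reader might also quote an excess of around 40%, but that needs rates near 47 to 50% in both arms, which the protocol does not plan for. Its own figures give 15% to 21%.

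The consequence is also limited. At the design effect both intervals exclude 1, and simulated power stays above the planned 80% even with the model-based variance. The error is conservative. The crude RR and the chi-square or Fisher test are planned separately and are not affected, and nothing says that the adjusted RR is the primary analysis.

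On covariates, biological plausibility is a stated criterion alongside significance. No passage says that IBFAT, weight change or admission will be adjusted for; they are listed as outcomes. The analyst works with coded groups, which limits deliberate steering.

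All of that stands. It does not answer the covariate rule. That rule is stated rather than left open, it brings significance in the trial data into the choice, and it names a different time point from the primary outcome. Coding the groups does not stop a mediator from being selected, because selection needs only its association with the outcome.

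**Conclusion.** The point holds for the adjusted analysis, at moderate weight.

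- **Firm, from the text alone:** the adjustment rule is unclear, draws on significance in the trial's own data, is screened at 6 months while the primary outcome is three or more months, and has no barrier against post-randomisation variables. That mediators would be adjusted for is a possibility the rule leaves open, not something the plan states.
- **Conditional on model-based variance:** log-scale intervals about 21% too wide at 24% vs 47.3%, and about 15% too wide at 24% in both arms, with type I error about 2.5% instead of 5%. This assumes that the 24% rate applies at three months. Exclusive feeding can only fall with age and the trial enrols mothers who intend to breastfeed, so the three-month rate may be higher and the excess larger; that too is an assumption.

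The RR itself is not biased by the variance choice, and the crude RR and its test are sound on this point. It would be wrong to conclude that the trial's main comparison is invalid.

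**What to change.** In Statistical methods, and to match in the abstract:

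- State that the adjusted RR is for exclusive breastfeeding for three or more months, from Poisson regression with robust (sandwich) standard errors (in Stata, `poisson` with `irr` and `vce(robust)`) or from a log-binomial model.
- State that the unadjusted RR is the primary analysis and the adjusted RR is supportive.
- Replace significance screening with a short list of pre-birth covariates already collected at entry, chosen on subject-matter grounds and fixed before unblinding. Maternal age and parity are examples, if the entry record holds them.
- State that no variable measured after birth enters the model.
- If the 6-month bivariate analysis is kept, label it exploratory and separate from the choice of covariates.

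The cost is one software option and a few sentences. Trials status says recruitment has not opened, so the change can be made before any data exist. The small downside is that a covariate found to be predictive later will not be in the main adjusted model; it can be shown in a sensitivity analysis.

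### The interim trigger of 106 is not half of the events expected after the planned loss: on the plan's own inputs it is the total expected without loss

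*Protocol article*

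**What the plan says.** The trigger appears twice in the protocol article. Statistical methods: "An interim analysis will be performed upon submission of half of the expected events (106"). Abstract, Methods/design: "An interim analysis will be performed upon the submission of half the expected events (106"). Both tie early-termination limits (Pampallona and Tsiatis) to this one look. Neither defines an event or gives the expected total.

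The inputs from which a total can be worked out are in the Sample size section. The baseline is given as "24 % babies in Colombia, received exclusive breastfeeding up to 5 months old", and the text adds: "This was the baseline risk assumed for the sample size calculation". The effect is "RR 1.97, 95 % CI 1.37 to 2.83". There are 150 newborns per group and an assumed loss of 30 %. The Hypothesis and Primary outcome sections make the outcome exclusive breastfeeding for three or more months.

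The closing paragraph of Statistical methods says that the data monitoring committee sees unblinded information and assesses "progress, safety data, and critical efficacy endpoints". It adds: "The information will be periodically revised every 2 weeks".

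**The concern.** An interim trigger is a decision threshold and has to be usable as written. Here the number next to the word half agrees with the whole expected count, and it takes no account of the loss the plan itself assumes. Two teams working from this text could run the look at 53 events or at 106, or wait for a count that never comes. Stopping limits set for a halfway look do not fit one made at 71 % or 99 % of the information, and a look near the end saves almost nothing.

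A second matter sits in the same section. The committee sees efficacy by arm far more often than the single look that carries limits, and the text does not say that those other reviews cannot end the trial for efficacy.

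**Working it through.** **Inputs** (Sample size section): control rate 0.24; RR 1.97, so the immediate-contact rate is 0.24 × 1.97 = 0.4728; 150 per group; 30 % loss, so 150 × 0.70 = 105 per group and 210 in all.

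**Can 106 be reproduced?** Expected events = n per group × (0.24 + 0.4728) = n × 0.7128.

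| | Control | Immediate | Total | Half |
|---|---|---|---|---|
| No loss, n = 150 | 36.0 | 70.9 | 106.9 | 53.5 |
| 30 % loss, n = 105 | 25.2 | 49.6 | 74.8 | 37.4 |

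The figure 106 matches the no-loss total, cut to a whole number. It is not the half in either row. For 106 to be the half, the total would have to be 2 × 106 = 212. That is 71 % of 300 infants (212/300) and more than all 210 expected to be evaluable.

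**Reading A: 106 is the trigger and the event is the primary outcome.**
- No loss: 106/106.9 = 99 % of expected events. From the exact sum of the two binomials, P(at least 106 events) = 0.57.
- 30 % loss: 106 is 42 % above the expected total (106/74.8 = 1.42). P(at least 106 events) is about 4 in a million.

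**Reading B: 106 is the total, so the trigger is 53.**
- No loss: 53/106.9 = 50 %. The arithmetic is right.
- 30 % loss: 53/74.8 = 71 %. The look is almost certain to occur, since P(at least 53 events) = 0.9997, but it comes late.

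**Reading C: the event is stopping before three months.**
- No loss: 300 − 106.9 = 193.1 expected, half 96.5; 106/193.1 = 55 %.
- 30 % loss: 210 − 74.8 = 135.2 expected, half 67.6; 106/135.2 = 78 %.

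**Sensitivity to the effect size** (primary-outcome events, limits of the quoted interval):
- RR 1.37: 150 × (0.24 + 0.3288) = 85.3 without loss; 59.7 with loss.
- RR 2.83: 150 × (0.24 + 0.6792) = 137.9 without loss; 96.5 with loss.

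After loss, 106 exceeds the whole expected count at both limits.

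**The case against.** The strongest reply is that the bracket directly follows the words for expected events and may simply give their total. That reproduces the figure from the stated inputs and the stated 150 per group, and a look at 53 will happen. This stands as a possible reading. It shows that the flat claim that the interim would never occur, or only at the end, goes beyond the text: that claim needs 106 to be the trigger itself and the event to be the primary outcome. It does not clear the sentence. The text does not say which reading is meant, and 53 still ignores the 30 % loss.

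It is also fair that the interim rule does not define the event. Reading C would bring the look before the end, though still not at half, and it departs from the outcome that the Hypothesis and Primary outcome sections name.

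Two stronger inferences are tempting and are not supported:
- **A head count mislabelled as events.** With a continuity correction the inputs give 74 per arm, and 74/0.70 rounds up to 106 per arm. The article mentions no such correction and plans 150 per group. The match may be chance, and the point does not need it.
- **Inflated type I error from fortnightly testing.** The text says that the committee assesses efficacy endpoints and that information is reviewed every two weeks. It does not say that efficacy is tested each time or that the trial could stop on it. Unblinded review by a monitoring committee is ordinary practice, and the content of its reports may be set in a charter not shown. What remains is a gap in wording, not a demonstrated error rate.

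**Conclusion.** The point holds. The stated trigger does not agree with the plan's own inputs, and no reading makes it half of the events expected after the planned loss. The look would come at 71 % of those events (106 as the total) or at 78 % (stopping as the event), or would practically never come (literal reading). Only reading 106 as the total and assuming no loss gives a true halfway look, at 53.

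These figures rest on the planning rates of 24 % and 47.28 %, on 30 % loss in both groups, and on the event being exclusive breastfeeding for three or more months. The 24 % is itself described as a rate up to five months, so the real three-month count may differ. That argues for a trigger that does not depend on an assumed rate.

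The monitoring point is secondary: stopping limits are tied to one look, while unblinded efficacy information is reviewed every two weeks with no statement that it cannot lead to stopping for efficacy.

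**What to change.** In both the abstract and Statistical methods:
1. Define the event for the interim rule as the primary outcome, exclusive breastfeeding for three or more months.
2. Replace 106 with a trigger at half information that allows for the planned loss: three-month status known for 105 of the 210 expected evaluable infants. Under the planning rates this corresponds to about 37 events. About 53 events is right only if no loss is assumed. Name one of these as the binding trigger; the count of infants is the safer choice because it does not move with the event rate.
3. If loss turns out below 30 %, the same trigger comes before halfway (105/300 = 35 % with no loss), so say that the limits will be computed at the information fraction actually reached.

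In the monitoring committee paragraph, state that early termination for efficacy can be decided only at this interim, and that the two-sided 5 % covers the interim and the final test together.

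The cost is a few sentences. No infants, visits or staff are added, and the Trials status section says that recruitment has not opened.
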